### Statistical analysis

The analysis will be based on intention-to-treat (ITT) using the “missing=failure” strategy. A robustness analysis, supported by the per-protocol approach, will be carried out if the patients present with protocol deviations (error of randomisation). Qualitative variables will be described by the percentages and numbers of each modality. Quantitative variables will be described by means and standard deviations. Confidence intervals at 95% will be presented.

A paper case report form (CRF) will be created for each patient inclusion for data collection and will be based on the establishment of a clinical database. All information required by the protocol must be provided in the CRF, necessary for statistical analyses.

To assess the primary endpoint (time to return to baseline heart rate and blood pressure), the mean values will be estimated by the Kaplan-Meier method (survival curves) and compared using Log-Rank tests. To assess the secondary endpoint (time to baseline O_2_ and change in measurements over time), the 2 arms will be compared in the same way as the heart rate and blood pressure parameters. Univariate and multivariate Cox models will be used to investigate the factors associated with the time to the baseline of cardiopulmonary constants. The difference in pain between D0 and D+3 will be compared between the 2 groups a Student’s *t*-test or a Wilcoxon test. Data for the analysis are collected from the first questionnaire (French version of Corah’s dental anxiety scale), the three phases of cardiopulmonary monitoring, the VAS assessment, and the postoperative questionnaire given to the patient at the end of the procedure. The information recorded on the postoperative questionnaire will be collected by a telephone call 3 days after the procedure. All the data collected will be typed and inserted into an Excel spreadsheet for data entry in a secure computer network of Nantes University Hospital. The investigative team, mainly the investigators as well as the study technicians involved in this study protocol will have access to the data collected.

In regard to the post-trial care, the patients will either continue their dental care with their appointed dentist, or in the case where they do not have one, they will be following appointments at the Nantes University Hospital.

A dissemination policy concerning the statistical data will be implemented to ensure that the official statistics are consistent, reliable, and comparable.

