### Design

This noninferiority, prospective, randomised, controlled, single-blind, two-group study will be conducted in the emergency subunits of the Nantes University Hospital. Eligible patients with irreversible pulpitis in the first or second mandibular molars requiring emergency dental care will be included in the study. Diagnosis will be based on clinical and radiographic examination. Two parallel groups will be randomised at a ratio of 1:1 so that patients will either receive (1) intraosseous anaesthesia or (2) inferior alveolar nerve block anaesthesia. This manuscript used the SPIRIT reporting guidelines [30].

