### Outcomes

The main outcome of this study is to compare the time required in minutes for the cardiovascular parameters to return to their initial values between the two techniques: ICA with the QuickSleeper™ system versus the reference technique: inferior alveolar nerve block (IANB). The timing of the evolution of the parameters is based on 3 phases: “baseline” from T0 to T+4 minutes, “anaesthesia” from T+4 to T+8 minutes, and “pulpotomy” from T+8 to T+14 minutes. The return to baseline values will be defined as a success if 3 successive values of heart rate and blood pressure (systolic and diastolic) are identical to those recorded before injection. On the other hand, if there is an absence of 3 successive values of these two parameters, it is defined as a failure.

Secondary outcomes include:The O^2^ measurement performed during the 3 phasesThe efficacy of the anaesthesia with a VAS (visual analogue scale) of 0 and that the pulpotomy was completed successfully: the patient is asked about his or her perception of pain before the operation at D0 and D+1, D+2, and D+3Post-operative careInvestigation of factors associated with delay in recovery of cardiovascular parameters (heart rate, dental anxiety, age, gender, and use of analgesics in the 6 h before surgery)

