### Determination of sample size

The sample size calculation was based on the noninferiority hypothesis in a pilot study that there will be an expected mean difference of 1 min 30 s between the two anaesthetic techniques with regard to the time taken for the values to return to the initial ones. According to the reported results from the few studies available, the proportion of patients having successful anaesthesia and better pain control in the reference group (intraosseous anaesthesia) would be 93%. The noninferiority margin was defined as 20%. The significance was set at 1.7% for the 3 main criteria (heart rate, systolic and diastolic blood pressure) and 5% for the secondary criteria. Thus, using a bilateral test with an epiR package 0.98-87 (Biostatgv), 72 patients (36 patients per arm) will be included in the study.

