### Protocol violations

All protocol violations occurring after randomisation will be listed in the clinical report form (CRF) and tabulated by the subject. The final assignment of participants to the per-protocol analysis will be decided at a blinded protocol review meeting before locking the database.

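### The non-inferiority conclusion rests on ITT with missing = failure, and per-protocol is a conditional extra with a narrow trigger; both choices can, but need not, favour similarity.

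*Protocol article*

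**What the plan says.** Under Design, the article describes the trial so: "This noninferiority, prospective, randomised, controlled, single-blind, two-group study will be conducted in the emergency subunits of the Nantes University Hospital". The Discussion adds that the aim is to conclude that recovery times are similar.

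Under Statistical analysis, the rule is: "The analysis will be based on intention-to-treat (ITT) using the “missing=failure” strategy". The per-protocol approach supports a robustness analysis that "will be carried out if the patients present with protocol deviations (error of randomisation").

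Under Protocol violations, the scope is wider: "All protocol violations occurring after randomisation will be listed in the clinical report form (CRF) and tabulated by the subject". Membership is then settled blind: "The final assignment of participants to the per-protocol analysis will be decided at a blinded protocol review meeting before locking the database".

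Under Outcomes, failure of the primary endpoint is defined: "if there is an absence of 3 successive values of these two parameters, it is defined as a failure". Under Statistical analysis, that endpoint is a time, for which "the mean values will be estimated by the Kaplan-Meier method (survival curves) and compared using Log-Rank tests".

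Nowhere does the article require ITT and per-protocol results to agree, and it gives no other rule for missing readings.

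**The concern.** In a superiority trial, counting missing as failure and analysing as randomised both tend to be cautious. In a non-inferiority trial, whatever makes the arms look alike helps the claim. Failures added equally to both arms shrink a real difference. Patients who received something other than the allocated technique alone, but are counted in their allocated arm, shrink it further.

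The usual safeguard is a per-protocol analysis that carries weight in the conclusion. Here it is conditional. On the wording under Statistical analysis, its trigger would miss the deviations that blur the arms most: the allocated technique not completed, or another technique added. At stake is whether a technique with slower recovery could be declared non-inferior more often than the nominal error rate allows.

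**Working it through.** **1. The two sections side by side.** Statistical analysis ties the per-protocol run to deviations, with randomisation error as the only gloss. Protocol violations lists every violation after randomisation and assigns per-protocol membership from them. The second is broader than the first. Neither makes the analysis unconditional or says what follows if it disagrees with ITT.

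**2. Direction of missing = failure.** Let the true success rates be p_ICA and p_IANB, and the missing shares m_ICA and m_IANB. The analysed rate in each arm is p(1 − m).
- Equal shares m: the difference d becomes d(1 − m). With d = 20 points, m = 10% gives 18 points and m = 20% gives 16.
- More missing in IANB (5% v 15%): 0.93 × 0.85 − 0.73 × 0.95 = 0.7905 − 0.6935 = 9.7 points, so ICA is favoured.
- More missing in ICA (15% v 5%): 0.93 × 0.95 − 0.73 × 0.85 = 0.8835 − 0.6205 = 26.3 points, so the rule is conservative.

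**3. Direction of mixing.** If a share c in each arm receives the other technique, ITT sees d(1 − 2c): 16 points at c = 10%, 12 points at c = 20%.

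**4. Illustrative size.**

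From the document: 36 per arm, a 20% margin (read as percentage points), and a success rate of 93%. The article attaches that rate to intraosseous anaesthesia and to anaesthetic success: "the proportion of patients having successful anaesthesia and better pain control in the reference group (intraosseous anaesthesia) would be 93" per cent. Outcomes, by contrast, names IANB as the reference technique.

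Assumed: IANB is the comparator at 93%, and ICA is worse by exactly the margin, at 73%. All missing and crossover rates are also assumed.

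Test: declare non-inferiority if p̂_ICA − p̂_IANB − z·√[p̂_ICA(1 − p̂_ICA)/36 + p̂_IANB(1 − p̂_IANB)/36] > −0.20 (unpooled Wald). The probability is found by exact binomial enumeration.

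| Scenario | One-sided 2.5% | One-sided 0.85% |
|---|---|---|
| No missing data | 3.3% | 1.6% |
| 5% missing, both arms | 3.6% | 1.5% |
| 10% missing, both arms | 4.0% | 1.6% |
| 20% missing, both arms | 5.7% | 2.3% |
| 5% ICA v 15% IANB | 17.0% | 8.8% |
| 15% ICA v 5% IANB | 0.5% | 0.2% |
| 10% two-way crossover, ITT | 7.9% | 4.1% |
| 20% two-way crossover, ITT | 16.3% | 9.1% |

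The 0.85% column is half the article's 1.7% level. The complete-data rows exceed nominal because of the Wald interval at this sample size, which is not the plan's choice.

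**5. The planned test.** A log-rank simulation used 2,000 runs, 36 per arm, exponential times and a 10-minute window, with missing patients kept as never returned. With assumed mean times of 2 v 3.5 minutes, the chance of detecting the slower technique at two-sided 1.7% falls from 48% to 18% with 10% missing in both arms, and to 10% with 20%. With 3 v 4.5 minutes it falls from 22% to 11% and 7%.

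**6. The planned sample size.** The stated 72 cannot be reproduced uniquely because power is not given. With 93% in both arms, a 20-point margin and two-sided 1.7%, the usual formula gives 68 at 80% power and 78 at 85%. Nothing above depends on how 72 was reached.

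**The case against.** **Missing data may be few and need not fall on IANB.** A reader might infer from the 44–81% block-failure range in the Background that IANB will lose more readings, and so take the 17% as the expected error. The article does not support that. A failed block does not remove the monitor, monitoring runs throughout the procedure, and the three phases span 14 minutes in one session. No missing rate is stated or implied, and the reverse imbalance gives 0.5%. With equal missingness of 5–10% the rise is small at 2.5% and absent at 0.85%. This objection stands, and it removes any claim that the error rate is known to be out of control.

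**The illustration is not the planned analysis.** The table tests a binary success difference, using an anaesthetic success rate, while the endpoint is recovery time compared by log-rank with no margin in the test. This also stands. The figures show direction and rough scale only. With an assumed 50% v 30%, the 5% v 15% scenario gives 8% rather than 17%.

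**Per-protocol may be broader than its parenthesis.** Read with Protocol violations, the deviations may include all violations, and with no deviations per-protocol equals ITT, so the condition would cost little. A reader might infer that no planned analysis could expose the dilution. That is too strong, because on the broad reading a per-protocol run would do so. What remains is that the two sections differ and that the result has no role in the conclusion.

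**Censoring is not a clean replacement.** If readings are lost because anaesthesia failed, censoring at the last valid reading assumes non-informative loss that may not hold. This stands, so censoring is proposed below as a sensitivity analysis only.

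**Conclusion.** The point holds in limited form. For a declared non-inferiority trial, the article fixes an analysis set and a missing-data rule that can favour similarity. It leaves per-protocol conditional, with a trigger narrower than its own section on violations and with no bearing on the claim.

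The direction is certain for equal missingness and for two-way mixing of techniques. For unequal missingness it depends on which arm loses more. The size cannot be stated from the document. Under the assumptions above, at nominal one-sided 2.5%, the error moves from 3.3% to between 0.5% and 17% across the missing-data scenarios shown, and to 7.9% or 16.3% with 10% or 20% crossover. Given the short single session, mixing of techniques may matter more than missing readings. This should be corrected, but the document does not show that the conclusion would be wrong.

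**What to change.** 1. Reconcile Statistical analysis with Protocol violations. Run the per-protocol analysis always, and define it beforehand to cover all major deviations after randomisation, including the allocated technique not completed and another technique added. Keep the blinded review to assign membership.
2. Claim non-inferiority only if ITT and per-protocol both support it.
3. Alongside missing = failure, report two sensitivity analyses for the primary endpoint. One censors at the last valid reading, with its assumption of non-informative loss stated. The other is an arm-specific worst case: missing ICA counted as not returned, missing IANB counted as returned.
4. Report missing readings and deviations by arm, so that the direction of any bias can be seen.

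The cost is revised wording and a few extra runs on data already collected. The downside is that the claim becomes somewhat harder to reach, since two analyses must agree with 36 patients per arm.

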Intra-osseous computerised anaesthesia (ICA), such as the QuickSleeper™ system (Dental Hi-Tec, Cholet, France), administers the solution with a computerised control into the diploë (a richly vascularized bone) at a local rate and pressure. Thus, the QuickSleeper™ system is a form of ID in which the anaesthetic is delivered close to the root apices and associated periradicular tissues, leading to a greater reduction in periradicular sensation. The anaesthesia takes effect more rapidly since the solution is deposited close to the apex of the tooth at an axis of 15° to 30°. Thus, this form of delivery increases its effectiveness and reduces the risk of tissue necrosis, with better pain control (42 to 93% according to studies) [22, 23]. No soft tissue numbness occurs, and relatively fewer amounts of anaesthetic solution are needed. However, due to the fast diffusion of the anaesthetic solution in the diploe, the heart rate accelerates via the added effect of vasoconstrictors. This elevation is transient, and its effect is negligible and does not pose serious cardiovascular risk [12, 22].

There are currently many clinical studies that have evaluated cardiac parameters during IO administration. The heart rate increases in a reversible manner depending on the speed of injection [12]. The Stabident™ system showed a significant increase in heart rate of 8-28 beats/minute (BPM) on average with 2% lidocaine 1:100,000 epinephrine according to 3 authors [24–26]. By comparison, the X-Tip injection elevated the heart rate by 9–10 beats per min [27]. In regard to other parameters such as oxygen saturation and blood pressure, Pereira et al found no differences in either of them when using the X-Tip™ system but noted a significant increase in heart rate with 4% articaine (1:100,000 or 1:200,000 epinephrine) for anaesthetizing irreversible pulpitis lower molars [23]. Therefore, the accelerated heart rate could be a potential adverse effect of this injection [27].

Articaine is a common anaesthetic agent and a member of the amide family. The presence of its thiophene group increases its liposolubility, facilitating its diffusion into both nerve sheaths (such as the inferior alveolar nerve) and neural membranes of individual axons comprising a nerve trunk. The lower pKa of articaine would translate into a greater percentage of the drug in the active base form and its plasma protein binding is 95% higher than most other local anaesthetics [25–27].

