### Interventions

The patient will be blinded to the affected group and will fill out the first questionnaire which is the French version of Corah’s dental anxiety scale [31] to assess his or her anxiety about dental care. Then, the patient will be placed with a cuff on the arm, and a pulse oximeter on the other finger connected to a blood pressure monitor to monitor the cardiovascular parameters (heart rate, systolic and diastolic blood pressure, and oxygen saturation) throughout the intervention.

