### Allocation concealment mechanism

As it is a randomised controlled study, the patients are blinded. The unblinding occurs if a patient decides to leave the protocol prematurely. The best care will be provided by the investigator and the pulpotomy will be performed under the best conditions to relieve the patient’s pain.

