## Discussion

Computerised intraosseous anaesthesia has gained considerable interest among practitioners in the last 25 years [32]. Wand® (Milestone Scientific, USA) was the first system used in 1997. What IO systems have in common is that the computer system controls the speed and pressure of the infiltration of the anaesthetic solution, to reduce pain, discomfort, and anxiety of the patient. Therefore, they are better alternatives to conventional bloc anaesthesia to counter IANB failure or as a first intention.

Vincent’s sign is the collateral effect of traditional IANB with ipsilateral lower lip anaesthesia, commonly used by clinicians as evidence of a successful anaesthetic procedure. However, this does not confirm that a successful pulpal anaesthesia has been obtained. Furthermore, accidental biting and burning of the lip and tongue (due to prolonged labial anaesthesia), as well as potential risks of mandibular nerve injury or a localised hematoma of the vascular lesion could occur. This further encumbers the advantages of this technique when comparing it to IO systems.

Very few valid clinical trials exist on the subject, most being realised with systems of intradiploid (ID) anaesthesia other than QuickSleeper™. Several studies have shown that supplemental Stabident™ ID injection, when added to IAN block and using local anaesthetics with vasoconstrictors, significantly increased the success of pulpal anaesthesia for 60 min [33].

One of the most important aspects of any primary anaesthetic technique is the pain experienced during the injection. This is particularly important for patients suffering from pain and stress due to an acute inflammation of the pulp. IANB, in particular, has been considered a fairly painful injection in the acute pulpitis situation. Owing to its asymmetric triple bevel, the needle tip in the QuickSleeper™ system makes possible a painless and easy perforation into the bone. The patient would report no pain or mild pain during perforation and solution deposition, despite the long wait for the agent to deposit. In addition, slow injection of more than a minute results in higher success rates [12, 22, 25]. The study by Özer has concluded that the pain levels after slow administration of QuickSleeper™ resulted in 82.5% success in mandibular third molars in assessing anaesthetic efficacy [29].

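### Missing = failure scores early leavers as never recovering, which cannot be assumed conservative for non-inferiority; add a log-rank censored at the last reading

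*Protocol article*

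**What the plan says.** All references are to the Protocol article.

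- **Statistical analysis**, missing data: "The analysis will be based on intention-to-treat (ITT) using the “missing=failure” strategy". The primary endpoint, time to return to baseline heart rate and blood pressure, is described by Kaplan-Meier curves and compared by log-rank tests.
- **Outcomes**, failure on that endpoint: "if there is an absence of 3 successive values of these two parameters, it is defined as a failure". The monitored phases run to T+14 min, with anaesthesia starting at T+4.
- **Allocation concealment mechanism**, early exit is foreseen: "The unblinding occurs if a patient decides to leave the protocol prematurely". The same section says that the pulpotomy is still carried out.
- **Interventions**, the equipment is there "to monitor the cardiovascular parameters (heart rate, systolic and diastolic blood pressure, and oxygen saturation) throughout the intervention".
- **Statistical analysis**, the one robustness analysis is per-protocol and "will be carried out if the patients present with protocol deviations (error of randomisation"). **Protocol violations** adds that a blinded review before database lock settles who belongs to the per-protocol set.
- **Design** declares non-inferiority, and the **Discussion** says the aim is to conclude that recovery times are similar.

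**The concern.** Read together, the missing-data rule and the definition of failure settle what happens to a patient who leaves before return and has no further readings. That patient stays in the risk set to the end of the window without an event, as if observed not to recover.

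In a superiority trial this treatment is often defended as cautious. That defence does not carry over to a trial meant to show similar recovery. Scoring leavers in both arms as non-recoverers makes the arms look more alike. Scoring more of them in one arm makes that arm look slower. The claim of similarity could thus be helped or hindered by who leaves, and no stated analysis would show by how much.

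**Working it through.** The plan gives no figure for exits or for the effect of the rule, so there is nothing of its own to reproduce. From the plan come 36 patients per arm, a two-sided 1.7% level, a difference of 1.5 min, and a window of 14 − 4 = 10 min. Return-time distributions, exit shares and exit times are assumptions.

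**1. Direction, in closed form.** Let p be the true share returned by the end of the window and e the share lost before return, unrelated to recovery. Under missing = failure the observed share is (1 − e)p. With equal e the observed difference is (1 − e)(p_IANB − p_ICA), so it always shrinks. Illustration with assumed return shares of 93% (IANB) and 73% (ICA), a true deficit of 20 points:
- 10% lost in both arms: 0.90 × 20 = 18 points.
- 10% lost in IANB only: 0.90 × 93 − 73 = 10.7 points.
- 10% lost in ICA only: 93 − 0.90 × 73 = 27.3 points.

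**2. Effect on the log-rank.** Exponential return times with means of 3 min (IANB) and 4.5 min (ICA), true hazard ratio 3/4.5 = 0.667 (below 1 means ICA is slower). A given share of each arm is prone to leave, at a time uniform over the 10 min. A return before exit counts. Simulated with 20,000 trials per row:

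| Prone to leave, IANB / ICA | Leave before return | HR, missing = failure | HR, censored at exit | Slower ICA flagged, missing = failure | Slower ICA flagged, censored |
|---|---|---|---|---|---|
| 0 / 0 | 0% | 0.660 | 0.660 | 23.2% | 23.2% |
| 10% / 10% | 3.5% | 0.679 | 0.660 | 19.9% | 22.0% |
| 20% / 20% | 6.9% | 0.689 | 0.659 | 17.8% | 21.9% |
| 40% / 40% | 13.9% | 0.707 | 0.661 | 14.6% | 19.5% |
| 30% / 10% | 6.3% | 0.778 | 0.658 | 8.5% | 21.5% |
| 10% / 30% | 7.4% | 0.608 | 0.662 | 31.9% | 21.5% |

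Hand check of the second column. P(exit before return) for a leaver is (m/10)(1 − e^(−10/m)), which is 0.289 for m = 3 and 0.401 for m = 4.5. At 10% / 10%: 0.10 × (0.289 + 0.401)/2 = 0.0345, or 72 × 0.0345 = 2.5 patients.

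With no true difference (3 v 3 min) and equal exits the hazard ratio stays at 0.999 to 1.000, so there is no bias. It moves to 1.120 at 30% / 10% and to 0.888 at 10% / 30%.

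**3. Can the documents fix the direction?** Suppose exits follow failed anaesthesia. IANB failure is 44 to 81% in irreversible pulpitis (Background), or 100 − 62 = 38% from the cited articaine trial. For intraosseous anaesthesia the Background says "with better pain control (42 to 93% according to studies"). Read as success rates, that is failure of 100 − 93 = 7% to 100 − 42 = 58%. The sample-size section takes the favourable end: "the proportion of patients having successful anaesthesia and better pain control in the reference group (intraosseous anaesthesia) would be 93"%. The Discussion cites a study that "resulted in 82.5% success in mandibular third molars in assessing anaesthetic efficacy", hence 17.5% failure. The ranges 38 to 81% and 7 to 58% overlap.

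Now assume exit at 4 to 7 min, return times starting 0 to 2 min after injection begins, and ICA truly 1.5 min slower. With full data 22 to 23% of trials flag it.
- IANB 44% v ICA 7%: 16 to 20% if a quarter of failures leave, 6 to 13% if all do.
- IANB 44% v ICA 58%: 22 to 23% in both cases.

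With no true difference (means of 4 min) and a quarter of failures leaving, the rule shifts the ICA minus IANB restricted mean by −0.05 to −0.08 min for 44% v 7%, which is at most 0.08 × 60 = 4.8 s. For 44% v 58% the shift is +0.02 to +0.03 min.

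**The case against.** **Exits may be rare or leave nothing missing.** The window is about ten chairside minutes, monitoring is planned throughout, and a patient who leaves the protocol still has the pulpotomy. If readings continue, the rule is never applied. This stands and is the main reason the point is minor.

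**The per-protocol review could remove leavers.** It could: Protocol violations is broader than the randomisation error named under Statistical analysis. But leavers are not named there. Excluding them also changes the population and leaves the missing-data rule as it is. So it would be wrong to say that no second analysis exists; none is stated to address this.

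**Censoring looks good by construction.** The simulations make exit independent of recovery. The Discussion links raised heart rate to fear, anxiety and symptoms, so patients leaving in distress may recover more slowly. Censoring would then be too kind to the arm that loses more. This stands, and limits censoring to a sensitivity analysis.

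**The return times are assumed.** Outcomes requires values identical to baseline. If few patients meet that, fewer leavers are wrongly scored and the effect is smaller. This also stands.

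**An article leaves sensitivity analyses to the SAP.** True, and a fuller plan may already contain this one. The rule itself, however, is stated here, and the point concerns what it does.

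**A stronger reading is tempting:** IANB fails more often, so the rule favours ICA. The documents do not support it. The failure ranges overlap, no exit rate is given, and nothing says that a failed injection leads to exit or that leaving stops the readings.

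**Conclusion.** The point holds as a minor one. As written, the rule counts an unrecovered leaver without later readings as never returned, and in this trial that cannot be assumed conservative. Its direction depends on the arm that loses more patients, and the documents do not settle which that is. The rule is conservative if ICA clearly loses more.

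The size is conditional. With about 3.5% leaving and both arms equally prone, the hazard ratio moves from 0.660 to 0.679 and detection of a slower ICA from 23.2% to 19.9%. Markedly unequal exits are needed for a large effect. Detection is low even with full data. These are log-rank rates under assumed exponential return times, not error rates against a non-inferiority margin.

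**What to change.** Keep missing = failure as the primary analysis and add to Statistical analysis:

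1. A return to baseline reached before exit stands. The times of exit and of the last reading are recorded.
2. A sensitivity Kaplan-Meier and log-rank analysis censors unrecovered leavers at their last reading. It is reported beside the primary analysis, with the number and timing of exits by arm.
3. If the two differ materially, the conclusion of similar recovery is not presented as robust.

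A formal rule that both analyses must show non-inferiority is not proposed, because no margin is stated on the time or hazard scale against which either could be judged.

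The cost is three sentences and one recorded time. Inclusion was due to end in July 2022, so the exit time may no longer be obtainable; the time of the last reading can serve. The drawback is that censoring may be informative, so the added analysis qualifies the primary one and does not replace it.
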